### Inclusion criteria

Adolescent girls aged 10–19 years who have mild or moderate anaemia (8 < Hb < 12 g/dl for girls aged ≥ 12 years and 8 < Hb < 11·5 g/dl for girls aged < 12 years) and consent to participate will be included in the study.

### Exclusion criteria

Adolescent girls who are pregnant/lactating, on anaemia treatment (Fe and folic acid supplements), severely anaemic (< 8 g/dl), severely underweight (BMI-for-age Z-score < −3 sd) and diagnosed with peptic ulcer or sickle cell disease will be excluded from the study. Severe anaemia is a life-threatening condition and requires immediate medical treatment in hospital^(33,34)^, hence the reason to exclude severely anaemic girls from the study. All the excluded severely anaemic girls will be referred to the hospital for treatment. Participants diagnosed with peptic ulcer are to be excluded because the spices (ginger, pepper and clove) in the beverage may irritate peptic ulcers. Additionally, ulcer bleeding might result in anaemia.

### Sampling procedure

A multi-stage cluster sampling technique will be employed in the study. Six communities in the district will be selected through simple random sampling. A school from each of the selected communities will be chosen through simple random sampling, making six schools in all. In the study schools (clusters), all adolescent girls in Upper Primary (Primary 4–6) and Junior High School will be screened based on the inclusion and exclusion criteria to identify eligible participants. Simple random sampling will be used to select the desired number of participants from the eligible participants. The study period is from February to October 2024. Figure 1 depicts the flow chart of the trial.

**Fig. 1. f1:**
[figure not shown]
Flow chart of the trial.

### Randomisation

An independent statistician will randomly assign the selected schools (clusters) to the 3 arms of study at a ratio of 1:1:1 (2 schools per arm) using the formula =RAND() in Microsoft Office Excel Software. Participants will be informed of their intervention allocation after baseline data collection is completed. This cluster randomisation method will prevent cross-contamination among the study arms through beverage sharing among participants^(35)^. Due to the nature of the intervention, blinding of participants and study team will not be possible; however, the data analyst will be blinded to the allocation of the participants.

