Fe deficiency is the main cause of anaemia among adolescent girls^(7)^. Adolescence is a period of fast growth with an acute rise in blood volume, lean body mass and red blood cell mass, which results in a surge in Fe requirement for the synthesis of Hb and myoglobin^(8)^. Adolescent girls are more vulnerable to Fe deficiency compared to their male counterparts because of the monthly loss of Fe through menstruation^(9)^. They are three times more likely to be Fe deficient as compared to adolescent boys^(6)^. Other factors such as poor bioavailability of dietary Fe, low dietary intake of Fe, infectious diseases and parasitic infections also contribute to Fe deficiency^(8,10)^. The determinants of anaemia are context-specific^(11)^, and in Ghana, some of the contextual determinants of anaemia include poor nutritional knowledge, intestinal worms, diarrhoea, food, malaria and poor dietary intake^(12)^. The diets of adolescents, particularly rural adolescents in Ghana, are largely plant-based^(13),^ and bioavailability of Fe from such diets is limited^(14)^; hence, most adolescent girls are unable to meet the increased Fe requirements during adolescence caused by high growth spurt and the loss of Fe each month through menstruation.

In Ghana, Fe food fortification and Fe supplementation are the main interventions in place to address Fe deficiency anaemia among adolescent girls^(15)^. However, these approaches have challenges in terms of acceptability, sustainability and affordability in developing countries^(16–19)^. Food-to-food fortification which utilises locally available foods is recommended as a good alternative measure for addressing micronutrient deficiency in developing countries, as it overcomes the aforementioned challenges of the conventional approaches^(16,17)^. Food-to-food fortification is the addition of a locally available and accessible micronutrient dense food to another locally available and accessible food to enhance the bioavailability of micronutrients to populations^(17)^. In Ghana, food-to-food interventions have been shown to improve Fe status of lactating mothers^(20)^ and anaemia status of children aged 6–9 years^(21)^. However, there is scanty data on food-to-food fortification interventions for improving the Fe status of adolescent girls in Ghana.

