### Study timeline

The protocol was developed from October 2022 to February 2023. Initial ethical approval and protocol amendment approval were obtained on 21st April 2023 and 10th January 2024, respectively. The treatment duration (Intervention) of the trial is six months. The specific timelines for participants’ enrolment, interventions, assessments, data analysis and dissemination of results are depicted in Table 1.

**Table 1. tbl1:** Schedule of enrolment, interventions, assessments, data analysis and results dissemination

	Study period								
	Enrolment	Allocation	Treatment period (6 months)						Close-out
Timepoint (t) (months)	*−t* _ *1* _	0	*t* _ *1* _	*t* _ *2* _	*t* _ *3* _	*t* _ *4* _	*t* _ *5* _	*t* _ *6* _	*t* _ *7–11* _
Enrolment:									
Eligibility screen	X								
Informed consent	X								
Allocation		X							
Interventions:									
Fortified beverage									
Unfortified beverage									
Fe-folate tablets									
Assessments:									
Socio-demographics	X								
Dietary intake	X								X
Anthropometry	X								X
Anaemia awareness and prevention	X								
Malaria testing	X					X			
Hb	X								X
Serum ferritin	X								X
C-reactive protein	X								X
Data analysis									X
Results dissemination									X

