##### Determination of haemoglobin status

Hb level of participants will be measured using URIT 12 Hb analyser^(65,66)^. The test strip will be inserted into the URIT 12 Hb analyser and a drop of the drawn whole blood placed on the sample spot of test strip. The Hb results will be recorded to the nearest 0·1 g/dl. For girls aged ≥ 12 years, Hb levels < 8 g/dl, 8–10·99 g/dl, 11–11·9 g/dl and ≥ 12 g/dl will be categorised as severe anaemia, moderate anaemia, mild anaemia and normal, respectively^(67)^. For girls aged < 12 years, Hb levels < 8 g/dl, 8–10·9 g/dl, 11–11·4 g/dl and ≥ 11·5 g/dl will be categorised as severe anaemia, moderate anaemia, mild anaemia and normal, respectively^(68)^.

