##### Determination of serum ferritin and C-reactive protein

The whole blood will be put in the gel-coated serum separator vacutainers and preserved at 4°C in an ice chest containing cold packs while in the field. The serum will be separated by means of a centrifuge at 500 rpm for 5 min at refrigerated temperature. The separated serum will be aliquoted and frozen at −80°C. The serum will be transported to the testing laboratory on frozen ice packs in an ice chest, when time is due for analysis. The ELISA technique will be used to assess serum concentrations of ferritin and C-reactive proteins. Fe deficiency will be defined as serum ferritin concentrations < 15 ug/l for healthy individuals and < 70 ug/l for individuals with inflammation/ infections^(55)^ and inflammation/infection as C-reactive proteins > 5 mg/l^(69)^.

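### Six schools are allocated by an unrestricted draw although school-level Hb is available first; ranking them into two strata of three would improve balance at almost no cost

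*Protocol article*

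**What the plan says.** Under Sampling procedure, six communities are drawn, and "A school from each of the selected communities will be chosen through simple random sampling, making six schools in all". The Randomisation section has an independent statistician assign these schools "at a ratio of 1:1:1 (2 schools per arm) using the formula =RAND() in Microsoft Office Excel Software". No restriction on the draw is described there or elsewhere in the article.

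The order of events comes from Table 1, "Schedule of enrolment, interventions, assessments, data analysis and results dissemination". Eligibility screening, socio-demographics, anthropometry, malaria testing, Hb, ferritin and C-reactive protein stand in the enrolment column, and allocation stands at time 0. The Randomisation section adds: "Participants will be informed of their intervention allocation after baseline data collection is completed". That sentence fixes only when the girls are told, so the order of allocation rests on the table.

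Hb would be known at once. In each school, "all adolescent girls in Upper Primary (Primary 4–6) and Junior High School will be screened based on the inclusion and exclusion criteria", and "Hb level of participants will be measured using URIT 12 Hb analyser", a test-strip device. Menarche status is among the general characteristics recorded at baseline. Ferritin is different: serum is frozen, and "The serum will be transported to the testing laboratory on frozen ice packs in an ice chest, when time is due for analysis", with no date given.

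Under Statistical analysis, the between-arm comparison of ferritin and Hb is a one-way ANOVA of means with Tukey's test. Regression appears only for relations between covariates and outcomes.

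**The concern.** Two schools per arm give randomisation little room to even out differences between schools. The introductory text after the abstract says that "The determinants of anaemia are context-specific" and names malaria, intestinal worms and diet among the Ghanaian causes. Each school comes from a different community, so such exposures can differ by school.

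If the two schools with the lowest Hb fall in one arm, the stated ANOVA has no baseline term to offset it. Six schools less three arms leave 3 between-school degrees of freedom, too few to adjust for several school-level factors afterwards. School-level balance is therefore better obtained in the draw, and the plan's own schedule supplies the data for it.

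**Working it through.** **The plan's own figure.** The article gives no probability of imbalance. Its sample size does reproduce. For ferritin, 2 × 20.1² × (1.96 + 0.84)² / 9.4² = 71.7, so 72. The design effect is 1 + 0.0009 × 42 = 1.0378. Then 72 × 1.0378 = 74.7, and × 1.15 = 85.9, so 86 per arm, or 43 per school.

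**Counting allocations.** Six schools into three labelled arms of two: 6!/(2! 2! 2!) = 90. Rank the schools on any one measure without ties.
- Two worst together: 18/90 = 1/5.
- Two best together: 18/90 = 1/5.
- Both at once: 3! = 6, so 6/90 = 1/15.
- Either: (18 + 18 − 6)/90 = 30/90 = 1/3.
- At least one of the two beverage arms holds such a pair: 22/90 = 24.4 %.
- One beverage arm holds the two worst and the other the two best: 2/90 = 2.2 %.

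**Turning rank into g/dl.** Between-school SD = √ICC × SD, with the plan's SDs of 1.2 g/dl (Hb) and 20.1 μg/l (ferritin). The ICC of 0.05 is an assumption; the expected ranges are simulated with 43 girls per school and normal school means.

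| | ICC 0.0009 (plan) | ICC 0.05 (assumed) | Planned effect |
|---|---|---|---|
| Between-school SD, Hb (g/dl) | 0.036 | 0.27 | 0.65 |
| Between-school SD, ferritin (μg/l) | 0.60 | 4.5 | 9.4 |
| Expected range of the three arm baseline mean Hb, unrestricted (g/dl) | 0.22 | 0.39 | 0.65 |
| Same, two strata of three (g/dl) | 0.14 | 0.25 | 0.65 |

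At the plan's ICC almost all of the 0.22 is sampling variation between girls: the SD of a school mean is √(0.0009 × 1.44 + 0.9991 × 1.44/43) = 0.19 g/dl, against a true between-school SD of 0.04.

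**What restriction gains.** Each arm mean averages two schools. Under a plain draw the SD of the arm 1 minus arm 2 difference is therefore √(1/2 + 1/2) = 1.00, in units of the SD of the school means being ranked.
- Two strata of three ranked schools, one per arm from each: 3! × 3! = 36 allocations, 0 of 36 with the two worst or two best together. The simulated SD is 0.65. For a factor correlated 0.5 with the ranking measure it is 0.92.
- Best-balanced 45 of 90 on one factor: 0.68. Best 30: 0.56.
- Best-balanced 45 of 90 on a joint score of three independent factors: about 0.83 for each. Best 30: about 0.77. For a factor correlated 0.5 with one of the three: 0.96 and 0.95.

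**The case against.** The strongest reply is that plain cluster randomisation is valid and unbiased, and that restricting it is a refinement. That stands. A reader might infer from the one-in-three figure that a third of allocations would damage the trial. The article does not support that: any six schools have a top two and a bottom two, however small the gaps, and at the stated ICC the true gaps in Hb are a few hundredths of a g/dl. Whether that ICC is credible is a separate question.

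The plan also acts against some of the suspected causes. All girls are dewormed before feeding and again midway, malaria is tested and treated at baseline and midway, and the analysis is also stratified by menarche status. These measures reduce school-level differences without removing them, for example malaria exposure between tests.

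Three further inferences should not be drawn:
- That all baseline data are in hand at allocation. This is secure for Hb and for rapid-test and questionnaire items, but not for ferritin, a primary outcome.
- That an Excel draw leaves no record. The article does not say whether the drawn values were fixed and archived, and a condensed article need not.
- That a permutation test over the restricted set would complete the remedy. For an overall three-arm statistic the labels are interchangeable, so the smallest attainable p is 6/90 = 0.067 even without restriction, 6/45 = 0.13 with half the set and 6/36 = 0.17 with two strata.

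**Conclusion.** The point holds as a cheap improvement to the design. The plan names an unrestricted draw of six schools, and its own schedule puts school-level Hb, malaria and menarche data ahead of that draw. One allocation in three pairs the two worst or the two best schools on a given ranking. Stratifying on mean Hb removes that pattern for Hb and lowers the SD of the beverage-arm difference in school mean Hb from 1.00 to about 0.65.

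The material benefit depends on the true ICC. It is small at 0.0009 and worth having at an assumed 0.05, where the expected range of arm baseline mean Hb falls from 0.39 to 0.25 g/dl against a planned effect of 0.65. It matters more because the stated ANOVA does not adjust for baseline. The figures assume that the formula is used to order schools into a fixed two-two-two split, that school means are roughly normal, and that 43 girls are taken per school.

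**What to change.** In the Randomisation section, replace the plain draw as follows. When baseline is complete in all six schools, the independent statistician ranks them on mean Hb of the selected girls, forms two strata of three, and randomly assigns one school to each arm within each stratum.

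As an alternative, score all 90 allocations jointly on mean Hb, malaria positivity and share post-menarche, drop the worse-balanced half, and draw one of the rest. This covers more factors, with a smaller gain on each (about 0.83 if they are independent).

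In the Statistical analysis section, adjust the between-arm comparisons for each girl's own baseline value. Do not add several school-level covariates: three would use up all 3 between-school degrees of freedom. Do not rely on a permutation test.

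The cost is a short paragraph and no new data. The downsides are that allocation waits for the last school's baseline, fewer allocations are possible, unmeasured factors gain little, and ferritin probably cannot be used for balancing. Two clusters per arm is not cured. The stated study period is February to October 2024; if allocation has already been made, what remains is to report school-level baseline values by arm and adjust for the girl-level baseline.

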### Study timeline

The protocol was developed from October 2022 to February 2023. Initial ethical approval and protocol amendment approval were obtained on 21st April 2023 and 10th January 2024, respectively. The treatment duration (Intervention) of the trial is six months. The specific timelines for participants’ enrolment, interventions, assessments, data analysis and dissemination of results are depicted in Table 1.

**Table 1. tbl1:** Schedule of enrolment, interventions, assessments, data analysis and results dissemination

	Study period								
	Enrolment	Allocation	Treatment period (6 months)						Close-out
Timepoint (t) (months)	*−t* _ *1* _	0	*t* _ *1* _	*t* _ *2* _	*t* _ *3* _	*t* _ *4* _	*t* _ *5* _	*t* _ *6* _	*t* _ *7–11* _
Enrolment:									
Eligibility screen	X								
Informed consent	X								
Allocation		X							
Interventions:									
Fortified beverage									
Unfortified beverage									
Fe-folate tablets									
Assessments:									
Socio-demographics	X								
Dietary intake	X								X
Anthropometry	X								X
Anaemia awareness and prevention	X								
Malaria testing	X					X			
Hb	X								X
Serum ferritin	X								X
C-reactive protein	X								X
Data analysis									X
Results dissemination									X

### Sample size

The formula employed for the sample size estimation is: N = 2S

(

+

/

^(36)^

where N is sample size

sd is standard deviation; estimated to be 20·1 μg/l for serum ferritin^(37)^ and 1·2 g/dl for Hb (anaemia)^(32)^.

 = 1·96 (From Z table) at a precision of 5 % and CI of 95 %.

 = 0·84 (From Z table) at 80 % power.

d is effect size; estimated to be 9·4 μg/l for serum ferritin^(38)^ and 0·65 g/dl for Hb (anaemia)^(39)^.

Sample size (Serum ferritin): N = 2

(

*+*

*/*

= 72

Sample size (Hb): N = 2

(

*+*

*/*

= 53

The larger sample size (N = 72) of the 2 variables (serum ferritin and Hb) will be used for the study.

As a cluster randomised controlled trial, cluster design effect has to be considered in the sample size calculation to improve the power and precision of the study^(40,41)^. The required sample size for a cluster randomisation trial is obtained by multiplying the sample size of the individual randomisation trial (N = 72) by the design effect^(42,43)^. Design effect = 1 + intra-cluster correlation (m-1), where m is the average cluster size. An estimated intra-cluster correlation of 0·0009^(44)^ will be used. The average size of each cluster (school) in the study district is estimated to be 55 adolescent girls, with the number of anaemic adolescent girls in each school estimated to be 43^(32)^, thus m = 43. Design effect = 1 + 0·0009(43–1) = 1·037. Hence, considering the design effect of 1·037 and 15 % attrition rate, the sample size will be 86 participants per arm (258 participants for the 3 arms, with 43 participants to be chosen from each school).

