### Statistical analysis

Data analysis will be done using Statistical Package for Social Sciences version 22 and WHO AnthroPlus software. Shapiro–Wilk and Kolmogorov–Smirnov tests will be done to test quantitative data for normality. Data that turns out not to be normally distributed will be analysed using non-parametric tests. Continuous data will be reported as means and sd, whilst categorical variables will be presented as frequencies and percentages. Data will be analysed using intention to treat analysis. One-way ANOVA will be used to compare means of serum ferritin and Hb levels among the three study groups (arms). Tukey’s post hoc test of one-way ANOVA will be performed to determine intergroup differences. Paired *t* test will be used to determine change in means of serum ferritin and Hb levels within groups (baseline and end-line). Relationship between covariates and outcome variables will be determined using multivariate linear and binary logistic regression analyses. WHO AnthroPlus software will be used to compute BMI-for-age Z-scores to determine participant’s nutritional status. Missing data will be resolved via multiple imputations. *P* < 0·05 will be considered significant at two-tailed tests.

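### The 80% power claimed for 86 girls per arm rests on normal quantiles and does not hold for a school-level comparison with two schools per arm

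*Protocol article*

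**What the plan says.** All figures are from the protocol article.

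- **Sample size.** The two-means formula is applied with "1·96 (From Z table") for the significance level and "0·84 (From Z table) at 80 % power". The ferritin SD is "estimated to be 20·1 μg/l for serum ferritin" with an effect of 9.4 μg/l. For Hb the SD is 1.2 g/dl and the effect 0.65 g/dl. The results are 72 (ferritin) and 53 (Hb), and the larger is taken. A design effect of 1.037 (ICC 0.0009, 43 girls per school) and 15% attrition lead to "the sample size will be 86 participants per arm", 258 in total. The section estimates 43 anaemic girls in each school.
- **Sampling procedure.** "A school from each of the selected communities will be chosen through simple random sampling, making six schools in all".
- **Randomisation.** Schools are the randomised units, "2 schools per arm".
- **Statistical analysis.** One-way ANOVA across the three arms, followed by Tukey's test. A P value below 0.05 "will be considered significant at two-tailed tests". No school term is stated for these comparisons.

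**The concern.** A design effect inflates the variance of an arm mean for clustering. It does not allow for how poorly that variance is known when it must be estimated from a handful of clusters. Six schools in three arms leave 6 − 3 = 3 degrees of freedom for between-school variation. One pair of arms taken alone leaves 2. Normal quantiles assume there are many.

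Readers will take the 80% as valid for a cluster trial, because the section says it has allowed for clustering. If the data are analysed at school level, the trial has roughly an even chance or less of detecting the planned ferritin difference. A null result against the unfortified beverage could then be misread as lack of efficacy, and a null result against Fe-folate as the similarity that the Introduction hypothesises. If the data are analysed by girl, as the Statistical analysis section describes, power stays near 80% when the ICC really is 0.0009. The exposure is then to false positives if the ICC is larger.

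**Working it through.** **Inputs.** The SDs, effects, ICC, attrition and numbers per arm are the protocol's. ICCs above 0.0009 are assumed, because the protocol gives no range.

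**1. Reproduce the plan.** N = 2·SD²·(1.96 + 0.84)²/d².
- Ferritin: 2 × 20.1² × 2.8²/9.4² = 71.7, so 72.
- Hb: 2 × 1.2² × 2.8²/0.65² = 53.4 (stated as 53).
- Design effect: 1 + 0.0009 × 42 = 1.0378.
- 72 × 1.0378 × 1.15 = 85.9, so 86.

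The plan's figures reproduce.

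**2. Precision after attrition.** Completers per arm: 86 × 0.85 = 73.1, or 36.55 per school. Design effect among completers: 1 + 0.0009 × 35.55 = 1.032. SE of a pairwise ferritin difference: 20.1 × √(2 × 1.032/73.1) = 3.38. Noncentrality: 9.4/3.38 = 2.78. For Hb the noncentrality is 3.22.

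**3. Power as the plan reckons it.** Φ(2.78 − 1.96) = 79.5% for ferritin, which matches the claim.

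**4. Power with between-school variance estimated.** Two-sided 0.05, noncentral t, critical value 3.18 (3 df) or 4.30 (2 df):

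| Outcome and condition | 3 df | 2 df |
|---|---|---|
| Ferritin, ICC 0.0009, after attrition | 48% | 35% |
| Ferritin, ICC 0.0009, no attrition (43 per school) | 54% | 39% |
| Ferritin, ICC 0, after attrition | 49% | 36% |
| Ferritin, ICC 0.01 (assumed), after attrition | 39% | 29% |
| Ferritin, ICC 0.05 (assumed), after attrition | 22% | 17% |
| Hb, ICC 0.0009, after attrition | 59% | 43% |

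A simulation of school means (200,000 runs, 37 girls per school, ICC 0.0009) gave 48.3% and 35.1% for ferritin. The ICC 0 row shows that the shortfall comes from the degrees of freedom and not from the size of the ICC. With Tukey's adjustment on 3 df the critical value rises to 4.18 and ferritin power falls to 30%.

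**5. Detectable difference.** At 3 df, 80% power needs a noncentrality of 4.26. For ferritin at ICC 0.0009 this is 4.26 × 3.38 ≈ 14.4 μg/l, against the planned 9.4. At ICC 0.01 it is 16.5 μg/l.

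**6. What ignoring school costs.** The type I error of an individual-level pairwise test is about 2·[1 − Φ(1.96/√DE)].
- ICC 0.0009: DE = 1.032, error 5.4%.
- ICC 0.01: DE = 1 + 0.01 × 35.55 = 1.36, error 9%.
- ICC 0.05: DE = 1 + 0.05 × 35.55 = 2.78, error 24%.

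**7. More girls or more schools (ferritin, ICC 0.0009).** With two schools per arm and 3 df, about 90 analysed girls per school would give 80%. Keeping 86 per arm but spreading them over four schools per arm gives 65% (6 df) to 71% (9 df) after attrition.

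**The case against.** The strongest reply is that if the ICC really is 0.0009, clustering is almost negligible. The planned individual-level comparison would then have about 80% power and a type I error of about 5.4%. That is correct. The fall to 35–48% is the price of estimating between-school variance from six schools instead of trusting an external ICC. But six schools cannot verify an ICC of 0.0009, and the section offers no sensitivity to it, so the 80% is conditional on a value the trial cannot check.

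It can also be said that adjusting for baseline would raise power. It might, but the protocol names no baseline adjustment for the between-arm comparison and gives no correlation from which to quantify the gain.

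Three stronger readings are tempting, and the documents do not support them.
- *The sample-size arithmetic is wrong.* It is not: 72 and 86 both reproduce. The fault is in the method.
- *No number of girls per school could repair the power.* At ICC 0.0009 about 90 analysed per school would do so (3 df). What stands in the way is the protocol's own estimate of 43 anaemic girls per school, all of whom are already planned for.
- *No randomisation-based test could reach P < 0.05.* Conditioning on one pair of arms gives 4!/(2!2!) = 6 allocations and a smallest two-sided P of 2/6 = 0.33. A three-arm statistic that ignores arm labels has 90/3! = 15 groupings and a smallest P of 1/15 = 0.067. But a labelled contrast of arm 1 with arm 2, referred to all 6!/(2!2!2!) = 90 allocations under the null of no difference among the three arms, can reach 2/90 = 0.022.

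**Conclusion.** The point holds as a fault of method in the Sample size section. The stated 80% power is not valid for a cluster comparison with two schools per arm. On the plan's own inputs, school-level power is about 48% or 35% for ferritin, the outcome that sets the sample size, and 59% or 43% for Hb (3 df or 2 df).

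These figures assume an unadjusted end-line comparison of two arms at two-sided 0.05, 15% attrition, an ICC of 0.0009 and between-school variance estimated from the trial. Retaining every girl raises ferritin power only to 54% or 39%.

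A reader might infer that the trial as planned has less than an even chance of a significant ferritin result. That does not follow for the individual-level ANOVA the protocol describes, which keeps near-nominal power at ICC 0.0009. Its weakness is an inflated false-positive rate if the ICC is larger. Either way, the Sample size section does not support a claim of 80% power with a valid 5% error rate unless the ICC is taken as known.

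**What to change.** In the Sample size section, restate the power for a school-level analysis using t quantiles with 3 df. Do this for both ferritin and Hb, over ICCs from 0.0009 to 0.05, with the attrition assumption stated. Say that about 14.4 μg/l of ferritin, not 9.4, is detectable with 80% power at ICC 0.0009, and that the figure is larger still with Tukey's adjustment. This can be done whether or not schools have been chosen, and costs only a less favourable figure.

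Optionally, if the schools are not yet fixed, spread the same 258 girls over more of them. Four schools per arm, with 86/4, about 22 girls each, gives about 65–71% for ferritin at ICC 0.0009 (6–9 df, after attrition). At an assumed ICC of 0.01 it gives about 59–64%. This adds school logistics and improves power without restoring 80%. The study period given under Sampling procedure is February to October 2024, so this option may no longer be open.

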### Study area

The study will be carried out in basic schools in Kumbungu District of Northern Ghana. In Ghana, the rural northern savannah agro-ecological zone has the highest prevalence of anaemia among adolescent girls (64·4 %)^(31)^, with the highest prevalence in the Kumbungu District (75 %)^(32)^.

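### The target of 43 girls per school equals the estimated number of anaemic girls in an average school, so there is no recruitment reserve; the attrition allowance is also slightly too small

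*Protocol article*

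**What the plan says.** The Sample size section of the protocol article derives 72 per arm for ferritin, multiplies by a design effect of 1.037, allows for 15 % attrition and arrives at 86 per arm, 258 in all, "with 43 participants to be chosen from each school". On the supply side it says: "The average size of each cluster (school) in the study district is estimated to be 55 adolescent girls", and it puts the anaemic girls among them at 43. That figure also serves as the cluster size m.

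Three other sections bear on the 43:

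- Inclusion criteria and Exclusion criteria admit only consenting girls with mild or moderate anaemia. They remove girls who are severely anaemic, pregnant or lactating, on iron-folate treatment, severely underweight, or diagnosed with peptic ulcer or sickle cell disease.
- Sampling procedure takes six schools, screens all girls in the relevant classes, and then says: "Simple random sampling will be used to select the desired number of participants from the eligible participants".
- Study area describes the savannah zone "with the highest prevalence in the Kumbungu District", at 75 %.

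**The concern.** The 43 estimated in the Sample size section counts anaemic girls, not eligible and consenting ones. The 43 required per school counts enrolled participants. Setting the two equal assumes that no anaemic girl is excluded and none refuses. A plan to sample at random from the eligible girls assumes the reverse, namely more eligible girls than places. The fixed number per school adds to the difficulty, because a school with more than 43 eligible girls cannot make up for one with fewer.

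At stake is the power stated for ferritin, the outcome that fixes the sample size. Any loss between anaemic and enrolled lowers it, and the attrition allowance, which is itself slightly short, cannot absorb that loss.

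**Working it through.** **Inputs (Sample size section unless noted).** Ferritin SD "estimated to be 20·1 μg/l for serum ferritin" and difference "estimated to be 9·4 μg/l for serum ferritin"; Hb SD 1.2 and difference 0.65 g/dl; z values 1.96 and 0.84; intra-cluster correlation 0.0009; m = 43; attrition 15 %; 55 girls per school. Six schools, two per arm (Sampling procedure, Randomisation). District prevalence 75 % (Study area). The intra-cluster correlation is taken as given here.

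**Reproducing 86.**

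- Ferritin: 2 × 20.1² × (1.96 + 0.84)² / 9.4² = 71.7, so 72.
- Hb: 2 × 1.2² × 2.8² / 0.65² = 53.4 (the protocol gives 53). Ferritin governs.
- Design effect: 1 + 0.0009 × 42 = 1.0378 (given as 1.037). 72 × 1.037 = 74.7.
- Attrition: 74.7 × 1.15 = 85.9, so 86. The stated figure is reproduced exactly, which shows that the allowance was multiplied on.

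**Attrition step.**

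- 86 × 0.85 = 73.1 per arm remain, against the 74.7 required.
- 74.7 / 0.85 = 87.8, so 88 per arm would be needed for 15 %.
- 1 − 74.7/86 = 13 %, the attrition that 86 tolerates.

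**Supply against demand.**

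- Demand: 86 × 3 = 258, which is 258 / 6 = 43 per school.
- Supply of anaemic girls: 6 × 43 = 258. The reserve is zero.
- Supply at the district prevalence: 55 × 0.75 = 41.25 per school, or 247.5 in six, about 10 fewer. By contrast 43/55 = 78 %.

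**Effect on power.** The protocol gives no exclusion or refusal rate, so the loss share is an assumption and is shown as a range. With share lost L:

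- enrolled per school k = 43 × (1 − L);
- evaluable per arm n = 2k × 0.85;
- design effect = 1 + 0.0009 × (k − 1), and n_eff = n / design effect;
- power = Φ[(d/SD) × √(n_eff/2) − 1.96].

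| L (assumed) | Enrolled, total | Evaluable per arm | Ferritin power | Hb power |
|---|---|---|---|---|
| 0 % | 258 | 73.1 | 79 % | 90 % |
| 5 % | 245 | 69.4 | 77 % | 88 % |
| 10 % | 232 | 65.8 | 75 % | 86 % |
| 20 % | 206 | 58.5 | 70 % | 82 % |

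Example, L = 10 %: k = 38.7; n = 77.4 × 0.85 = 65.8; design effect = 1 + 0.0009 × 37.7 = 1.034; n_eff = 63.6; (9.4/20.1) × √31.8 − 1.96 = 0.68; Φ(0.68) = 0.75.

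The first row is the attrition slip alone. If each school has 41 anaemic girls, as the district prevalence implies, and all enrol, then 82 × 0.85 = 69.7 per arm are evaluable and ferritin power is about 77 % before any exclusion or refusal.

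**The case against.** A reader might infer that 258 cannot be reached from six schools at all. The Sample size section does not support that: 6 × 43 is exactly 258, so on its own estimate the target is attainable with no losses. Nor does the 75 % figure settle the matter. Both prevalence figures carry the same citation, and 75 % against 78 % may reflect rounding, averaging over schools or a different denominator. It is a mismatch for the authors to reconcile, not proof that the pool is 248.

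A reader might also infer that the random selection step cannot work. The 55 and 43 are district averages, and in any school with more than 43 eligible girls the draw works as written. It has nothing to select from only in schools at or below the average.

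The attrition slip is small: two girls per arm and under one percentage point of ferritin power. The protocol states no evaluable number, and 74.7 is derived here. The slip should not be read as a failure of the design. Hb, the other primary outcome, stays above 80 % throughout the range shown.

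Reserve or replacement arrangements may be set out in a full protocol that is not shown, and their absence from the article is not the criticism. What stands is that the article itself fixes the number required at its own count of anaemic girls, before its own eligibility and consent rules apply.

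**Conclusion.** The concern holds as a lack of reserve, not as an impossibility. The target of 258 is met only if every anaemic girl in six average schools passes the exclusions and consents. Any loss puts enrolment below target and ferritin power further below the stated 80 %: about 77, 75 or 70 % for losses of 5, 10 or 20 %. Those shares are assumptions. The power figures also rest on the protocol's own SD, difference, intra-cluster correlation and 15 % attrition. The attrition arithmetic is a separate, minor error: 86 per arm allows about 13 %, and at 15 % power is about 79 %.

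The two points meet in one place. Raising the target to 88 per arm would ask for 44 girls per school, more than the 43 anaemic girls estimated. Restating what 86 can bear is therefore more coherent than raising the target.

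**What to change.** 1. In Sampling procedure and Sample size, replace the 43 per school and the random draw with enrolment of every eligible, consenting girl in each selected school. Larger schools can then offset smaller ones. This does not create girls in an average school, so the next step is needed as well.
2. Restate expected enrolment as the anaemic pool times an explicit eligible-and-consenting share, and give the resulting power for ferritin and Hb over a plausible range of that share.
3. Reconcile 43 of 55 (78 %) with the 75 % in Study area, and use one figure in both places.
4. State that 86 per arm allows about 13 % attrition.

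The cost is recalculation and rewording, a less favourable stated power, some extra supplies in larger schools, and unequal school and arm sizes. With two schools per arm, one large school could unbalance the arms noticeably, so the restated power should use the expected arm sizes.
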